#### Psychosocial Behavior and Life Events

Parents will be requested to provide information about their own socio-economic background, their child's stress exposure and psychosomatic complaints via a questionnaire. Parents will complete two separate instruments to report their children's stress levels. To assess recent critical life events, parents/guardians should complete a 16-item adapted version of the *Life Events Checklist* (58). Parents should rate the impact of each event on their child's life, using a 4-point scale from 0 (no impact) to 3 (large negative impact). The mean influence of all events will be calculated as a trauma indicator. Thus, children with few life events with a strong influence could have higher scores compared to subjects with several but moderate life events. In addition, three sub-scales (family, friends, and school) of the KINDL^R^ questionnaire (59) will be used to assess specific sources of stress in the lives of the participating school children. Parents will be asked to respond on a 5-point Likert scale ranging from 0 (never) to 4 (all the time). The sub-scales used in this study were family (e.g., “my child got on well with us as parents,” “we quarreled at home”), friends (e.g., “my child got along well with his friends,” “my child felt different from other children”), and every day functioning at school (e.g., “my child easily coped with schoolwork,” “my child worried about his/her future”). Positively poled items will be recoded before computing the sub-scale mean scores, so that higher scores reflected increased psychosocial stress throughout all dimensions.

### Biological Sampling and Biochemical Analysis

#### Urine Sampling and Analysis

On the day before participation, a set of questionnaires, instructions for urine collection, all consumables for urine collection and information on the following day's measurements will be given to the child to take home after school. The following morning (day of participation), the participant is requested to collect a first voided morning midstream urine sample in the privacy of their own home with assistance from their parents. The filled urine container is then placed in the provided small cooling container with an ice pack. Urine samples are then collected at the schools and delivered to the laboratory for preparation according to standard procedures and stored in −80°C bio freezers prior to further analysis. Urinary biomarkers will be measured from stored urine samples including standard and novel biomarkers related to arterial modulation and nutrition. Initially, urinary albumin, creatinine, chloride, sodium, potassium, nitrite, nitrate, symmetric and asymmetric dimethylarginines, dimethylamine, malondialdehyde, and targeted metabolics will be measured.

#### Salivary Sampling and Analysis

On the day of participation in physical fitness assessments, each participant will be asked to provide a fasting saliva sample in provided SaliCaps (IBL International GmBH), before 8 am. Two additional saliva samples will be collected; one before the 20 m shuttle run test and another 30 min after the shuttle run intervention. This is done for a hypothalamic-pituitary adrenal axis reactivity intervention on cortisol levels, known to be involved in the harmful effects of stress exposures on cardiovascular function and biological aging (60). We will determine the salivary cortisol and estrone levels using solid phase enzyme-linked immunosorbent assays (ELISA) with the Synergy HT microplate reader, BioTek.

### Data Capturing, Management and Integrity

The ExAMIN Youth SA study will make use of the REDCap (Research Electronic Data Capture) system to capture all data elements. REDCap is a free, secure web-based, and user-friendly electronic database software which can be quickly developed and customized for studies for collecting and tracking information and data from research studies and scheduling patient visits (61). Each participant will receive a unique number linked to their data with no direct association to their personal information. A dedicated Data Manager ensures the correct handling of confidential information and provides anonymous and password protected datasets to the researchers using the data for analyses.

### Proposed Analysis

#### Sample Size Calculation

We aimed to include 20 urban schools from the [name] district with a conservative calculation of 60 children participating per school, leading to a total sample size of ~1,200 children over a period of 19 months. However, with dropouts or school absentees we expected a total sample size of ~1,000 participants. Using G^*^Power version 3.1.9.2 (62), we determined the required effect size (*f*
^2^ = 0.025) for a given 2-sided level alpha error of probability at 0.05, in a total sample size of 1,065 and ten predictors for fixed model linear multiple regression analysis with blood pressure or pulse wave velocity or arteriolar-to-venular-ratio as main outcomes. With the proposed sample of 1,065 children, we achieve 95.3% power.

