### Outcomes

The study has the following outcomes based on primary school children in the North West province of South Africa:

To evaluate obesity and hypertension prevalence along with its determinants motor skills and physical fitness/activity, intake from food groups, and psychosocial behaviors.To assess the association of body mass index and blood pressure with central pulse wave velocity and retinal vessel diameters in South African children.To identify whether the associations of arterial modulation with physical fitness/activity, intake from food groups, and psychosocial behaviors are dependent on ethnicity.

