### Setting of the Study

The study sites where data collection is performed are located within the [name] district in two of the southern municipal areas namely JB Marks (Potchefstroom) and Matlosana (Klerksdorp) (Figure 2). The majority of the population in these areas consist of black (82%), with the remainder comprising of 14% white, 4% mixed-race, and 1% Indian, as reported on wazimap.co.za (accessed on 16 August 2019). All the data collection procedures are conducted in a school-based setting with the endorsement and support of the District Director's office of the Department of Education.

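### The stated 95.3% power fits about 1,000 children, not 1,065, and belongs to an overall test of ten predictors; it does not carry over to the ethnicity outcome

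*Protocol article*

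**What the plan says.** The Sample Size Calculation section plans for about 1,200 children from 20 schools and then says that "with dropouts or school absentees we expected a total sample size of ~1,000 participants". The model behind the power calculation is a "fixed model linear multiple regression analysis with blood pressure or pulse wave velocity or arteriolar-to-venular-ratio as main outcomes". Its inputs are f² = 0.025, N = 1,065 and ten predictors, and the error level is described as a "2-sided level alpha error of probability at 0.05". The section concludes: "With the proposed sample of 1,065 children, we achieve 95.3% power". No other power figure is given, and the section does not say whether f² refers to the whole model or to one coefficient.

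The Outcomes section lists three aims. The second concerns the associations of body mass index and blood pressure with pulse wave velocity and retinal vessel diameters. The third is "To identify whether the associations of arterial modulation with physical fitness/activity, intake from food groups, and psychosocial behaviors are dependent on ethnicity". The Statistical Analysis section plans multiple linear regression to estimate the change in outcome per unit of each determinant, with 95% confidence intervals.

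On ethnic mix, the Setting of the Study section describes the local population: "The majority of the population in these areas consist of black (82%), with the remainder comprising of 14% white". No expected mix for the sample is given.

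**The concern.** A single power figure that stands beside a list of outcomes will be read as applying to all of them. Two features make that unsafe here. First, the figure does not match the N printed next to it. Second, the hypothesis behind it (that ten predictors jointly explain some variance) is not one of the listed outcomes. Calling alpha two-sided suggests a test of one coefficient and hides this, because an overall F test has no such sidedness.

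The third outcome is where it matters. It is a comparison of slopes between ethnic groups, which is less precise than a slope estimated in the whole sample. A reader who applies 95% power to it could give a non-significant interaction more weight than the data can bear.

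**Working it through.** **Inputs from the Sample Size Calculation section.** f² = 0.025, alpha = 0.05, ten predictors, N = 1,065 (stated) or about 1,000 (expected), stated power 95.3%.

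**Step 1: reproduce the stated figure.** For the overall F test in a fixed-model regression, numerator df u = 10, denominator df v = N − 11, and noncentrality λ = f² × N. Power is the probability that a noncentral F(u, v, λ) exceeds the 5% critical value.

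| N | λ | Power |
|---|---|---|
| 1,000 | 0.025 × 1,000 = 25.0 | 95.35% |
| 1,065 | 0.025 × 1,065 = 26.6 | 96.6% |
| 1,200 | 0.025 × 1,200 = 30.0 | 98.3% |

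Solving for N at exactly 95.3% gives about 998. Rounding of f² does not close the gap at N = 1,065: f² = 0.0245 still gives 96.2%, and 95.3% would need f² of about 0.0234. The difference is 96.6 − 95.3 = 1.3 percentage points, and the printed figure is the lower one.

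**Step 2: which test is it?** For one coefficient in the same ten-predictor model (u = 1, f² = 0.025), power is 99.9% at either N. That is not near 95.3%, so the stated figure is the omnibus one.

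**Step 3: individual associations.** The partial f² that gives 80% power for one coefficient is approximately (1.96 + 0.8416)² / N.
- N = 1,065: 7.849 / 1,065 = 0.0074.
- N = 1,000: 7.849 / 1,000 = 0.0078 (0.0079 by the noncentral F).

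The article gives no partial f² for any single determinant. For assumed values of 0.0025, 0.005 and 0.01, power at N = 1,065 is 37%, 64% and 90%.

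**Step 4: dependence on ethnicity.** The assumptions here are mine. There are two ethnic groups with shares p and 1 − p, the exposure and the residual each have SD 1 in both groups, and children are independent. The standard error of the slope difference is then √[1/(Np) + 1/(N(1 − p))], with N = 1,065.
- p = 0.5: √(4/1,065) = 0.0613.
- p = 0.14: Np = 149.1 and N(1 − p) = 915.9, so √(0.006707 + 0.001092) = 0.0883.

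As the difference, take the slope equivalent to f² = 0.025 in one group and zero in the other: √(0.025/1.025) = 0.156 SD per SD. Power is close to Φ(difference/SE − 1.96), and the detectable difference at 80% power is 2.80 × SE.

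| Assumed mix | Power, difference 0.156 | Power, half that (0.078) | Detectable at 80% power |
|---|---|---|---|
| 50:50 | Φ(2.55 − 1.96) = 72% | 25% | 2.80 × 0.0613 = 0.17 |
| 14% white | Φ(1.77 − 1.96) = 42% | 14% | 2.80 × 0.0883 = 0.25 |

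None of these figures allows for clustering of children within schools. The article gives no intra-school correlation.

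**The case against.** The mismatch in N is small and conservative: the design as stated has slightly more omnibus power than is claimed, and for the expected number of about 1,000 the figure is right. That stands, and it makes the pairing a correction rather than a threat to the study.

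A reader might go further and infer that the individual associations are underpowered. The documents do not support that. With equal f², the single-coefficient test has more power than the omnibus test, and 80% power is available down to a partial f² of about 0.0074 before clustering. Power of 37% arises only if f² = 0.025 is split equally over ten predictors, and nothing in the article says so.

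A reader might also infer that the study has little chance of detecting an ethnic difference. That too goes beyond the text. The 14% is a share of the local population, whereas the sample consists of volunteers from selected schools, and at an even mix the power is 72% for the assumed contrast. What can be said is that the interaction power depends on an effect size and a mix that are not given, and that over the assumed range it lies below 95%.

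Nor were the wrong outcomes powered. Pulse wave velocity is the stiffness measure, and the arterio-venous ratio is computed from the two retinal vessel diameters.

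Finally, this is a condensed article. Power for each aim may stand in the full protocol or analysis plan, and the Statistical Analysis section already promises confidence intervals. This limits the point to what is printed: one figure, with the wrong N and an unlabelled hypothesis. Nothing in the article says that a non-significant interaction would be read as no difference.

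**Conclusion.** Wrong as written, at modest cost. Two findings follow from the article's own inputs: 95.3% belongs to about 1,000 children (1,065 gives 96.6%), and it is the power of the overall ten-predictor test rather than of a coefficient or an interaction. The first has little consequence. The second means that 95% cannot be quoted for the ethnicity outcome. The sizes given for that outcome, 72% and 42%, are illustrations that rest on an assumed slope contrast of 0.156 against zero, an assumed two-group mix, standardised scales and no clustering. Main-effect associations are not shown to be at risk.

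**What to change.** Rewrite the power paragraph.
1. Pair the figures correctly: 95.3% at N = 1,000, or 96.6% at N = 1,065.
2. Label the result as the overall F test of all ten predictors and drop the two-sided description for it.
3. Add the detectable single-coefficient effect at 80% power (partial f² of about 0.0074 at N = 1,065), with an allowance for school clustering.
4. Add the detectable ethnicity slope difference at 80% power for the sample mix actually expected. Before the design effect this is about 0.17 SD per SD at 50:50 and about 0.25 at 14% white.
5. Do not present 95% as the power for the ethnicity outcome. Report the interaction estimate with the confidence interval already promised.

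The cost is one reworded paragraph and no extra children. The downside is a less favourable stated power for the third outcome.

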#### Statistical Analysis

The IBM^®^ SPSS^®^ Statistics software (Armonk, NY: IBM Corp.) will be used for data analysis. The 95% confidence intervals will be presented for measures of effect to indicate the amount of uncertainty. For future analysis, normality will be assessed by visual inspection using normal QQ plots. If residual plots indicate deviation from model norms, logarithmic transformations of the outcome variables will be considered. To describe continuous characteristics, we will use median and interquartile ranges or means and standard deviations; and for binary variables, we will use percentages by performing chi-square tests. To estimate absolute changes in outcome variables for one unit increase of determining factors, multiple linear regression analysis will be applied.

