### Recruitment and Informed Consent or Assent

The children are recruited from public schools, however heterogeneity in terms of socio-economic background is inevitable in the South African context. The Principal Investigator received endorsement and approval from the Department of Education to approach the school principals to present the project and discuss the details of each measurement and the purpose of the study. A school teacher, not directly involved with the particular children, will be identified as the mediator. Handout letters are circulated to the parents/caregivers to indicate their participation. Parents are invited to address any questions to the research team in order to make an informed decision and give parental permission for their child to participate in the study. All the relevant documentation including an informed consent/assent will then be provided to interested families. When the child along with the parents agree to participate, they will be requested to complete the informed consent/assent forms along with a battery of questionnaires prior to participation, and provide further consent/assent on the day of measurements.

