The study does have some general limitations to report. The cohort will include volunteers as the children will not be randomly selected to participate. All children from the selected schools will be invited to participate and those with permission and consent from their parents and who gave assent will be included. The screening sites include only two (of three) municipality areas in one (of four) districts in the North West province of South Africa, making this cohort not representative of the whole province or the country. The accessibility to children younger than 5 years of age is extremely challenging and therefore we will include children between 5 and 9 years of age as these are the youngest ages at which we can observe potential signs of early vascular aging and potential health disparities among the groups to be studied in our cohort. With the ethical challenges to obtain blood samples from children, especially in a school-based setting, we will only obtain urine and saliva samples from the participants. With the stable nature of urine, we are able to measure a large number of metabolites and biomarkers which could aid in risk stratification and prospective risk prediction. The ExAMIN Youth SA study will generate new knowledge and contribute to the current limited data available, especially in an African context, on childhood health and in particular the interplay of physical inactivity, body composition, dietary behavior, and psychosocial determinants on micro- and macrovascular outcomes. The prospective nature of this observational cohort study will allow us to investigate potential identifiers of early cardiovascular risk in South African children by assessing target organ damage markers after 4-year of follow up and determine the predictors assessed in baseline. In addition, we have the opportunity to cross examine our main outcomes with a center in Basel, Switzerland with a similar cohort (22) of 6–8 year old children and identify similarities and differences of early vascular aging determinants between African and European children.

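### Children are recruited in about 20 schools, but the 95.3% power and the named analyses treat them as independent; how much this matters depends on an intraclass correlation the article does not give

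*Protocol article*

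**What the plan says.** Under Sample Size Calculation the article sets a school-based target: "We aimed to include 20 urban schools", "with a conservative calculation of 60 children participating per school, leading to a total sample size of ~1,200 children", with about 1,000 expected after dropout and absence. The Discussion confirms that whole schools are approached: "All children from the selected schools will be invited to participate".

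The same sample size paragraph then computes power "in a total sample size of 1,065 and ten predictors for fixed model linear multiple regression analysis", with effect size f² = 0.025 and alpha 0.05, and reports 95.3%. It mentions no ICC, design effect or inflation.

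Under Statistical Analysis the model is "To estimate absolute changes in outcome variables for one unit increase of determining factors, multiple linear regression analysis will be applied". Binary variables are handled by percentages and chi-square tests, and 95% confidence intervals are promised for measures of effect. No school term, random effect, estimating equation or robust variance is named. The limitations in the Discussion cover volunteering and representativeness, not clustering.

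**The concern.** Children of one school tend to resemble each other, and each extra child from a school already sampled then adds less information than a child drawn independently. The article itself says that "heterogeneity in terms of socio-economic background is inevitable in the South African context". It does not say how much of that variation lies between schools, but some similarity within schools is a reasonable expectation.

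If outcomes are positively correlated within schools, formulas for independent observations give standard errors that are too small. The error is greatest for prevalences and for predictors that differ mainly from school to school. At stake are the intervals around obesity and hypertension prevalence (first listed outcome), the type I error of some regression coefficients, and the meaning of the 95.3%.

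**Working it through.** **Inputs from the article (Sample Size Calculation).** 20 schools; N = 1,065; ten predictors; f² = 0.025; alpha 0.05; stated power 95.3%. Average school size m = 1,065/20 = 53.25.

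**Assumed, because not given.** Outcome ICC 0.01 to 0.10; predictor ICC 0.05 to 1 (1 means constant within school); prevalence 12.5%. That last figure is the proportion of elevated blood pressure which the Background cites for black boys in an earlier study, used here only as an illustration.

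**Step 1: reproduce the stated power.** The overall F test of ten predictors has 10 and N − 11 degrees of freedom and noncentrality N × f². With independent children:
- N = 1,065: noncentrality 26.6, power 96.6%.
- N = 1,000: noncentrality 25.0, power 95.35%.
- The test of a single coefficient at N = 1,065 gives 99.9% and does not match.

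The stated figure is therefore an overall F test on independent observations. It fits N = 1,000 more closely than 1,065, but the gap is small and I do not treat it as a separate error.

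**Step 2: how much clustering the 95.3% tolerates.** It needs an effective sample of about 1,000, so a design effect of at most 1,065/1,000 = 1.065. Setting 1 + (53.25 − 1) × ICC = 1.065 gives ICC = 0.065/52.25 ≈ 0.0012. For a predictor that varies within schools, the same limit applies to the product of predictor and outcome ICCs.

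**Step 3: power with predictors measured per child.** Design effect DE = 1 + 52.25 × ICC(predictor) × ICC(outcome); effective N = 1,065/DE; power as in Step 1. As an approximation, all ten predictors share one ICC. Coverage of a nominal 95% interval is 2Φ(1.96/√DE) − 1.

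| Predictor ICC / outcome ICC | DE | Effective N | Power | Actual coverage |
|---|---|---|---|---|
| 0.05 / 0.02 | 1.05 | 1,012 | 95.6% | 94.4% |
| 0.1 / 0.05 | 1.26 | 844 | 90.6% | 91.9% |
| 0.3 / 0.05 | 1.78 | 597 | 74.9% | 85.8% |
| 1 / 0.01 (limiting case) | 1.52 | 700 | 82.9% | 88.8% |
| 1 / 0.05 (limiting case) | 3.61 | 295 | 38.7% | 69.8% |

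The last two rows require every predictor to be constant within school. Changing m makes little difference: at ICC 0.01 in the limiting case, power is 83.9% with m = 50 and 80.8% with m = 60.

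**Step 4: prevalence.** A prevalence carries the full DE = 1 + 52.25 × ICC. The half-width under independence is 1.96 × √(0.125 × 0.875/1,065) = 1.96 × 0.01013 = 2.0 points.
- ICC 0.01: 2.0 × √1.52 ≈ 2.5 points (2.6 with t on 19 degrees of freedom).
- ICC 0.05: 2.0 × √3.61 ≈ 3.8 points (4.0 with t on 19 degrees of freedom).

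**Step 5: type I error of ordinary regression.** Simulation with 20 schools of 53 children, a random school intercept, 2,000 replicates, ethnicity ICC 0.3 to 0.8 and exposure ICC 0.05 to 0.2, at a nominal 5%:

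| Outcome ICC | Ethnicity main effect | Exposure-by-ethnicity interaction |
|---|---|---|
| 0.01 | 6–9% | 5–6% |
| 0.05 | 11–22% | 5–8% |
| 0.10 | 16–34% | 5–10% |

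Exposure slopes that vary between schools would raise the interaction column; that was not simulated.

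**The case against.** The strongest objection is that this is one condensed paragraph in a journal article, and that variance estimation is commonly left to an analysis plan, which may exist unseen. That is fair for the analysis model, and a later plan could add a school effect. It does not rescue the power figure, which is fixed in the article, in the same paragraph as the school-based design, and is reached only under independence.

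A second objection is that the size is unknown. This stands. There is no ICC in the article, 20 schools is a target, and no method for prevalence intervals is fixed, so Step 4 describes what happens if the ordinary binomial formula is used.

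Three stronger readings are tempting and are not supported:
- **Power collapses to 39% or lower.** That needs all ten predictors to be constant within school. The determinants listed under Outcomes (fitness and activity, food groups, psychosocial behaviours, body mass index, blood pressure) are measured per child.
- **The third outcome suffers type I error of up to a third.** That outcome asks whether associations depend on ethnicity, which is an interaction. The high figures belong to an ethnicity main effect, and only if ethnicity clusters by school.
- **Ethnicity, diet and socio-economic status differ strongly between schools, and children of a school share a measurement day and team.** These are plausible, but the article does not state them.

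**Conclusion.** The point holds in conditional form. Recruitment is clustered in about 20 schools, while the stated power and the named analyses assume independent children, and nothing in the article accounts for the difference. The 95.3% is valid only if the relevant ICC, or product of ICCs, is about 0.001 or less.

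Above that limit the consequence depends on the quantity estimated. For child-level predictors it ranges from negligible to moderate (power 95.6% to 75% over the cases shown). For prevalences, half-widths are about a quarter larger at ICC 0.01 (√1.52 = 1.23) and nearly double at ICC 0.05 (√3.61 = 1.90). For predictors that differ mainly between schools, type I error can rise well above 5%; for the interaction in the third outcome the rise is smaller. All of this rests on assumed ICCs, equal school sizes and a random school intercept. If the true ICC is near zero, the results would barely change.

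**What to change.** - **Regressions:** fit a linear mixed model with a random intercept for school and small-sample degrees of freedom (Satterthwaite or Kenward-Roger), or keep linear regression with cluster-robust standard errors and a small-sample correction for about 20 clusters.
- **Binary variables and prevalences:** replace plain chi-square tests by school-clustered methods, such as mixed logistic regression or modified Poisson regression with cluster-robust standard errors. Compute prevalence intervals with school as the cluster and 19 degrees of freedom.
- **Power:** replace the single 95.3% by a range over stated predictor and outcome ICCs, as in Step 3.
- **Reporting:** give the observed ICCs of the main outcomes.

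School means of the exposures are not needed to correct the standard errors. With ten predictors they would use about 10 of the 19 between-school degrees of freedom and would address contextual effects that are not among the listed outcomes.

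The cost is a change of wording and of analysis code. The named SPSS software fits mixed models, and no new data are needed provided that school is recorded for each child, as school-based recruitment suggests. The price is wider intervals and a less favourable power figure.
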